## Abstract

**Introduction:**

Adolescents and young adults (AYAs) affected by cancer are an understudied group. Effective interventions are needed to support coping with the late effects of cancer, its treatment and to promote quality of life. Nature-based interventions may be promising in support of the self-management and health of AYAs affected by cancer. However, randomised controlled studies (RCTs) on the effectiveness of such interventions are lacking. We performed a first pilot RCT (n=42) that showed that it is feasible and safe to conduct such a study. Here, we propose a full-scale RCT to investigate the effectiveness and safety of a wilderness programme on the mental and physical health of AYAs affected by cancer.

**Methods and analysis:**

Participants are 150 AYAs affected by cancer, aged 16–39 years, who will be randomised to a wilderness (n=75) or a hotel stay (n=75). The wilderness programme is an 8-day intervention including a 6-day wilderness expedition. This is followed 3 months later by a 4-day intervention including a 2-day basecamp. Activities include hiking, backpacking, kayaking, rock climbing, mindfulness and bush-crafting. The comparison group is an 8-day hotel stay followed by a 4-day hotel stay (interventions include two travel days) at the same hotel after 3 months. Primary outcomes are psychological well-being and nature connectedness up to 1 year after the study start. Secondary outcomes are quality of life, physical activity and safety parameters.

**Ethics and dissemination:**

The Swedish Ethical Review Authority approved the study protocol on 27 September 2023 (reference: 2023-05247-01). The recruitment started on 19 February 2024 and the first part is planned to end on 31 December 2027. Study results will be disseminated by means of scientific publications, presentations at conferences, popular articles, interviews, chronicles and books. News items will be spread via social media, websites and newsletters.

**Trial registration number:**

ISRCTN93856392.

STRENGTHS AND LIMITATIONS OF THIS STUDYThe feasibility of this randomised controlled trial design has previously been piloted.This study will be carried out by a multidisciplinary research team with strong support from patient and public involvement.This study aims to investigate the long-term health effects of a wilderness programme.This study will include a heterogeneous cancer study population.Comparison to no programme participation or a wait-list control will not be included in this randomised controlled trial.

## Introduction

Adolescents and young adults (AYAs) affected by cancer, either by a childhood or AYA cancer diagnosis, are a growing but understudied population.^1^ Due to cancer or its treatment, many AYAs experience at least one late effect such as psychosocial problems, concentration/memory difficulties and fatigue that negatively impact their quality of life.^2^ Furthermore, they suffer disproportionately from chronic diseases and have an excess risk for early mortality compared with non-cancer populations.^3^ It appears that AYAs affected by cancer receive little follow-up care that appropriately addresses these late effects.^2^ Consequently, different self-management strategies have evolved by which they are trying to cope with late effects. These include pushing themselves physically and mentally to master everyday activities, balancing social activities and rest, and recuperating and regaining energy.^4^ Other coping strategies reported are seeking distraction, support from family and friends, yoga or meditation, or changes in lifestyle such as increased physical activity and healthy diets.^5^ Although AYAs affected by cancer acknowledge the importance of these self-management strategies in dealing with the late effects of cancer or the cancer treatment itself, it remains an ongoing challenge.^5^ Therefore, it is a high priority to find effective interventions that support the self-efficacy of AYA impacted by cancer, thereby minimising the negative impact of cancer-related late effects and improving their quality of life.^5^

Physical activity-based interventions have been shown to increase physical activity and reduce fatigue in childhood cancer survivors.^6–8^ However, results must be interpreted with caution due to the small sample sizes and large heterogeneity among the reviewed studies.^7^ Physical activity-based interventions have also been reported to increase the quality of life of AYA cancer survivors, however, with marginal significance.^9^ It appears to be difficult for AYAs affected by cancer to return to or maintain adequate levels of physical activity, and they seem to make little use of existing supporting physical activity services within the community.^10^ A number of barriers exist that make it more difficult to engage in physical activity including self-reported fears about health, low baseline activity levels and/or fitness, lack of motivation, cancer-related pain or fatigue, age at diagnosis, anxiety about health and lack of advice from a physician.^11 12^

Another promising intervention in support of the self-management of cancer survivors is nature-based interventions. Those affected by cancer have reported that engaging with nature is important for their health and well-being.^13–15^ Research from different fields indicates that nature-based interventions may decrease anxiety, depression, stress, tension, fatigue, pain and improve sleep in those affected by cancer.^16^ Nature may provide a safe space and motivational context for patients with cancer that supports relaxation, recovery, physical activity and may ignite reflection, inspiration, personal growth and supportive relationships.^14 17 18^ Furthermore, it has been demonstrated that spending time in nature leads to more frequent or longer stays in nature.^19^

To gain insight into the possible beneficial effects of nature-based interventions specifically for AYAs affected by cancer, we first performed a scoping review on the topic.^20^ Nature-based interventions such as adventure and wilderness programmes were found to increase self-efficacy, self-esteem, self-confidence, physical activity and social support among AYAs affected by cancer. However, it was found that randomised controlled trials (RCTs) on the effectiveness of nature-based interventions were lacking. Other gaps identified were the lack of studies on the long-term effects (>3 months) of nature-based interventions and lack of data on the safety of these interventions.^20^ Therefore, in 2021–2022, we performed a pilot study to investigate whether it would be feasible to perform an RCT design on a nature-based intervention.^21^ For this pilot study, we developed a Wilderness programme for AYAs (WAYA programme) affected by cancer. The WAYA programme is grounded in Næss’s ecosophy^22^ and the Positive Health Model.^23^ A detailed description and schematic outline of the WAYA programme theory and content has previously been published.^24^ We demonstrated that it was feasible and safe to conduct a pilot RCT.^25^ None of the 42 AYAs that participated in the interventions dropped out of the study, and adherence to programme interventions and data completeness after 1-year follow-up was high. The WAYA programme was found to be just as safe for AYAs affected by cancer as a hotel stay. The relative frequency of reported adverse effects (AE) was similar in both study arms (relative risk (RR) 1.0, 95% CI 0.8 to 1.3), and all AEs were non-serious, mild or moderate of severity, and resolved during the study period.^25^ Furthermore, the WAYA programme appeared to be acceptable, developmentally appropriate and of interest to AYA affected by cancer.^24 25^ Based on these observations, we recommended for a future larger RCT to (1) apply additional recruitment strategies for participants, (2) to stratify for the inclusion of cancer survivorship (childhood cancer vs AYA cancer), (3) to optimise the content of the WAYA programme and (4) to select health-related outcomes based on the lived experiences of participants in the WAYA programme.^26^

The aim of this study is to perform a full-scale multicentre RCT (WAYA-2 study) that investigates the effectiveness and safety of a wilderness programme on the mental and physical well-being of AYAs affected by cancer. The WAYA programme and WAYA-2 study protocol have been optimised according to the findings and recommendations from the pilot study as described above.

## Methods and analysis

### Study guidance and design

The WAYA-2 study protocol is developed in line with the Standard Protocol Items: Recommendations for Interventional Trials (SPIRIT) 2013 guidance for protocols of clinical trials and the SPIRIT 33-item checklist.^27^ The WAYA-2 study will be conducted in accordance with the guidelines of the Declaration of Helsinki, and results will be reported according to the Consolidated Standards of Reporting Trials, 25-item checklist and flow diagram.^28^ This is a multicentre RCT in Norway and Sweden with a two-armed parallel design using individual randomisation. A quantitative RCT design will allow the testing of active aspects of a complex wilderness intervention including physical activity, physical challenges, experiential activities, being in nature and other reflective practices. A hotel stay is chosen as a comparison to control for other possible effective factors such as attention, group support and getting out of their regular environment.

### Research questions

The following research questions will be addressed:

Does a wilderness programme, including a wilderness expedition and basecamp stay:

Increase psychological well-being of AYAs affected by cancer compared with a control activity.Increase nature connectedness of AYAs affected by cancer compared with a control activity.Improve health-related quality of life of AYAs affected by cancer compared with a control activity.Increase physical activity level of AYAs affected by cancer compared with a control activity.Is a wilderness programme equally safe for AYAs affected by cancer as a hotel stay (control activity)?

### Participants and inclusion criteria

Participants are adolescents and young adults aged 16–39 years that have been diagnosed with any type of cancer during childhood, adolescence or young adulthood. Another inclusion criterion is the ability to walk 2 km a day (walking aids or assistance from another person is permitted). Participants with various disabilities such as mobility, vision and hearing impairments, balance problems and special treatment or dietary needs can be included. Prior experience with outdoor activities is not required for study participation.

Exclusion criteria are as follows:

Cancer treatment imposes unwanted risks for AYAs on programme participation, as evaluated by their treating physician/oncologist.A medical condition of AYAs that prevents safe travel to, or participation in the programme, as evaluated by their treating physician/oncologist.Not willing to be randomly assigned to programme interventions.Previous participation in the WAYA-1 study.

Following the recommendations of AYA cancer experts in our advisory board, we will deliberately refer to participants in the WAYA-2 study as AYAs affected by cancer, rather than childhood and AYA cancer survivors.

### Intervention group: wilderness programme

The development of the WAYA programme affected by cancer has previously been published.^24^ The WAYA programme aims to increase physical activity, self-confidence, self-efficacy and self-care, to support personal growth and building meaningful relationships, and to provide an enjoyable and safe stay in nature. Nature in the WAYA programme has both a contextual and an active role in support of the health and well-being of AYAs affected by cancer, wherein their health is regarded to be intrinsically interwoven in a bidirectional fashion with the health and well-being of nature.^29^ Participants are given the opportunity to experience a diversity of natural landscapes, and specific nature characteristics are actively incorporated in programme activities. Activities in the programme include hiking, sea-kayaking, backpacking, rock climbing and camping. The programme also includes (nature) reflective practices such as mindfulness, meditation and forest bathing.^24^ Outdoor skills taught include mapping/compass/orienting, trail cooking, safety training, equipment planning, foraging, fishing, bush-craft skills and leaving no trace. The wilderness programme consists of three intervention parts: (1) An 8-day intervention that includes 2 days for travelling and physical testing and a 6-day wilderness expedition; (2) A 3-month in-between period where participants are contacted once every month online to coach them to engage in their own outdoor activities and (3) A 4-day intervention including a 2-day base camp programme. Both the expedition and basecamp programme will take place in natural settings around the High Coast of Sweden or in Southern Norway. The group size will be 10–12 participants, and the facilitator–participant ratio will be 3:10. The 6-day wilderness expedition will be logistically supported by a team of 5–7 volunteers.

### Control group: hotel stay

The hotel stay will be for 8 days at a Spa Hotel in Sweden or Norway, including 2 days for travelling and physical testing and a 6-day hotel stay, followed by a second 4-day stay at the same hotel (including two travel days) 3 months later. Similar to the wilderness intervention, during the 3-month in-between period, participants will be contacted once every month to ask how they are doing. The content of the hotel stay includes the following activities: Spa facilities, museum visits, watching television/movies, playing games/gaming, shopping and fine dining. Participants will engage in organised group activities, but this does not include any nature-based activities. The group size is 10–12 participants, and the facilitator–participant ratio will be 3:10.

### Program facilitators

In Sweden and Norway, we will work with professional teams of outdoor instructors and facilitators who have previous experience in wilderness programmes with young cancer survivors or other vulnerable youth populations. Facilitators of the WAYA programme have competence in one or more of the following areas: outdoor life, survival, nature/wilderness guiding, kayaking, climbing, nursing, first aid, (youth/group) counselling/supervising, mindfulness, mind-body techniques and data collection for research purposes.^24^ At least two facilitators of the WAYA programme are licensed health professionals (nurses, psychologists) and at least one facilitator of the WAYA programme and hotel stay is an AYA affected by cancer. For programme intervention fidelity, referring to the degree to which the WAYA programme is performed in a similar manner in Sweden and Norway, two members of the Norwegian outdoor team will join the Swedish outdoor team for the first wilderness intervention in Sweden and vice versa. For supervision of participants in the hotel stay, facilitators will have competence in guiding/supervising groups, first aid and research methodology for data collection and safety monitoring.

### Outcomes

The selection of outcomes is driven by the aims of the WAYA programme and recently published qualitative study results of the WAYA programme.^26^ The aims of the WAYA programme and underlying process to support self-realisation via nature connectedness are hypothesised to contribute to a chain of actions that impacts the six domains of Positive Health.^25^ The WAYA programme is a complex intervention and may potentially impact multiple factors. Therefore, in line with guidance and instructions for RCTs on complex interventions, more than one primary outcome is chosen in relation to the research questions.^30^

#### Primary outcomes (confirmatory)

Changes in psychological well-being of AYAs affected by cancer over time, measured by the Psychological Well-being Scale (PWS).^31^ This scale consists of six domains: self-acceptance, positive relations with others, autonomy, environmental mastery, purpose in life and personal growth. Together, these dimensions can contribute to the assessment of a person’s level of positive functioning and well-being. This instrument is translated and validated in the Swedish context.

Rationale: Significant and relevant changes in the PWS have been demonstrated for complex interventions including mindfulness-based programmes.^32^ The PWS was not included as an outcome measure in our previous pilot study,^1^ but based on the findings from the qualitative study of the WAYA programme, we have selected PWS as a primary outcome measure.^26^ For the qualitative analysis of the pilot study, participants in the wilderness programme were interviewed at 3 months after start of the programme to explore the impact of the programme on their health and well-being. The themes that arose through the inductive content analysis related to self-confidence, self-acceptance, meaningful relationships and personal growth. These themes are also reflected within the domains of the PWS providing additional richness to the data.^31^

Changes in nature connectedness of AYAs affected by cancer over time, measured via the Nature Relatedness Scale (NRS).^33^ The NRS is a 21-item scale that measures the ‘affective, cognitive and physical relationship individuals’ have with the natural world. For the purpose of the previous pilot study,^25^ the NRS was translated and validated in the Swedish language (results not published).

Rationale: In line with guidance and instructions for RCTs on complex interventions,^30^ nature connectedness is hypothesised to be the underlying mechanism (intermediate outcome) along the theorised impact path towards eudaemonic (psychological) well-being. A significant increase in NRS has previously been demonstrated in childhood and AYA cancer survivors after participation in the WAYA programme compared with the hotel stay.^25^

#### Secondary outcomes (exploratory)

Secondary outcomes explore possible changes in quality of life, physical activity and fitness:

Changes in quality of life of AYAs affected by cancer over time, measured by the Minneapolis Manchester Quality of Life instrument (MMQL).^34^ The MMQL is a quality-of-life questionnaire specifically designed for cancer survivors and consists of seven quality of life domains: physical functioning, cognitive functioning, psychological functioning, body image, social functioning, intimate relations and outlook on life. The instrument is translated and validated in the Swedish context.Changes in light and moderate-to-vigorous intensity physical activity will be measured objectively using ActiGraph.^35^
Changes in maximal oxygen consumption (VO2max; mL/kg/min) will be estimated by means of the Ekblom Bak cycle ergometer test.^36^
Blood pressure and heart rate will be assessed with an electronic monitor in a seated position after a 5 min rest. Two measurements will be performed, and the lowest value will be registered.Body mass index (BMI) will be measured non-fasted and in light clothing to the nearest 0.1 kg by a digital scale. Height will be measured to the nearest 1 mm by a stadiometer. BMI (kg/m^2^) will be calculated.

Considering the large similarity between the Swedish and Norwegian language, the validated Swedish primary outcome scales (PWS, NRS and MMQL) will only be translated to the Norwegian language and back translated for quality control.

#### Safety-related outcomes

An occurrence of (serious) AEs during the interventions is reported and documented in the field diaries. AEs will be coded according to the Medical Dictionary for Regulatory Activities^37^ and analysed using preferred terms and allocation to system organ class. The safety of the programmes will be evaluated by analysing the number, seriousness, intensity and types of AEs that are evaluated to be certain, probable/likely or possibly related to the study programmes. Equal safety between the wilderness programme and hotel stay is defined as no significant differences in the risk of having serious AEs on wilderness versus hotel stay participation.

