### Sample size

The current study aims to recruit a total of 150 participants who will be randomised into two groups (n=75 per group). The power calculation is based on a two-group linear mixed-effects model for repeated measures data with attrition^38^ and provides 80% power to detect a medium-sized between-group difference (SMD=0.60). In the sample size estimation, we account for an attrition rate of 34.5% before the start of the intervention as reported in the previous pilot study^25^ and a low attrition rate (10%) during the intervention. The power calculation is based on a model with four repeated measurement points, a first-order autoregressive correlation structure, an initial repeated measures correlation of 0.60 (with decreasing magnitude of the repeated measures correlations with increasing distance between time points), an alpha level of .05, and a group allocation of 1:1.

The effect size estimates for the primary outcomes are based on a meta-analytical estimate^32^ of a standardised between-group difference of 0.69 (Hedges’ g) for interventions to enhance eudaemonic psychological well-being, and findings from a pilot study indicating a significant between-group difference in NRS between the wilderness programme and hotel stay (Cohen’s d=0.63).^25^

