### Data analysis

χ^2^ statistics, independent samples t-tests and analysis of variance will be used to calculate group differences in sociodemographic variables and cancer characteristics at baseline. The alpha level will be set to 0.05. The primary analysis will investigate changes in the total scores of the PWS and NRS over time from baseline to 1- year follow-up in the intervention group compared with the control group. Missing data will be imputed by means of multiple imputations or by using full-information maximum likelihood estimation.^41^ The analysis of the primary outcome will be based on a linear mixed-effects model and will be fitted to test intervention effects up to 1 year. Adjustments will be made for age, gender, age at cancer diagnoses and study site. Time, intervention arm, interaction between time and intervention arm, age, gender, age at cancer diagnoses and study site are included as fixed effects, and the participant is included as random effect in the model. Statistical analyses will be on the intention-to-treat principle (all participants who are randomised in the study). As sensitivity analyses, the per-protocol data set will be analysed including only participants who have participated for at least 1 day in the wilderness or hotel stay. Secondary outcomes will also be analysed using linear mixed-effects models.

Categorical data will be presented as frequencies and percentages. For continuous data, the number, mean, SD, median, IQR, minimum and maximum will be calculated. A two-sided p<0.05 will be considered statistically significant.

Safety analyses will be performed on the safety analysis set and include all individuals who had participated in one of the programme interventions for at least 1 day. RR with 95% CI will be calculated to indicate the risk of having an AE adjusted to days of exposure to programme interventions. Pearson’s χ^2^ test will be used to calculate differences in AEs severity between the two study arms. A detailed description of the planned statistical analyses will be provided in the statistical analysis plan, which will be finalised prior to database closure and data analysis. All statistical analyses will be performed by using Stata V.18.0.

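### Equal safety is defined as a non-significant difference in serious AEs, with no margin; at the low rates the pilot suggests, this rule would nearly always return 'equally safe'

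*Protocol article*

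**What the plan says.** The last research question in the protocol article is "Is a wilderness programme equally safe for AYAs affected by cancer as a hotel stay". The Safety-related outcomes section fixes how it will be answered: "Equal safety between the wilderness programme and hotel stay is defined as no significant differences in the risk of having serious AEs". Under Data analysis, "A two-sided p<0.05 will be considered statistically significant". No equivalence or non-inferiority margin and no expected serious-AE rate is given.

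The Sample size section plans to "recruit a total of 150 participants who will be randomised into two groups (n=75 per group", which "provides 80% power to detect a medium-sized between-group difference (SMD=0.60". That calculation concerns the primary outcomes; safety does not enter it.

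Data analysis also plans an exposure-adjusted relative risk (RR) with 95% CI for having an AE, and Pearson's chi-square for AE severity. The test for serious AEs is not named. Of the pilot, the Introduction reports that "all AEs were non-serious, mild or moderate of severity"; 42 people took part.

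**The concern.** A non-significant result means that the data did not rule out equality. It does not show that a harmful difference has been ruled out. With rare events and small arms, non-significance is the expected result whether or not the programmes differ. The rule also rewards weak information: a smaller trial, or more loss before the start, makes a finding of equal safety more likely.

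Safety is part of the stated aim, and the Discussion says the results will inform participants, families and clinicians. A doubled or tripled serious-AE risk could therefore be published as equal safety under a rule set in advance.

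**Working it through.** **1. The plan's own sample size.** For a standardised difference of 0.60, two-sided alpha 0.05 and 80% power, n per arm = 2(1.960 + 0.842)² / 0.60² = 43.6, rounded up to 44. Allowing for 34.5% loss before the start and 10% during the intervention, 44 / (0.655 x 0.90) = 74.6, or 75 per arm and 150 in total. This simple formula reproduces the stated figure, and no safety input is needed to reach it.

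**2. Size of the safety set.** It requires at least one day of participation. With the plan's 34.5% loss before the start, 75 x 0.655 = 49.1, about 49 per arm. The most favourable case, no loss before the start, is 75 per arm.

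**3. Observed splits that count as equal safety.** Two-sided p-values at 49 per arm with no serious AE in the hotel arm:

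| Wilderness v hotel | Fisher p | Pearson p (uncorrected) |
|---|---|---|
| 3 v 0 | 0.242 | 0.079 |
| 4 v 0 | 0.117 | 0.041 |
| 5 v 0 | 0.056 | 0.022 |
| 6 v 0 | 0.027 | 0.011 |

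Under Fisher, 5 v 0 (10% v 0%) is still equal safety. Under Pearson, 3 v 0 (6% v 0%) is, but 4 v 0 and 5 v 0 are not. The same 5 v 0 result would thus be labelled differently depending on a test that the protocol article does not name.

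**4. How often the rule declares equality.** Exact enumeration: sum Bin(x; n, pW) x Bin(y; n, pH) over all pairs (x, y) with p ≥ 0.05. All true rates are assumptions. Cells show Fisher/Pearson.

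| True risk, hotel v wilderness | 49 per arm | 75 per arm |
|---|---|---|
| 1% v 2% | 99.97% / 99% | 99.8% / 97% |
| 1% v 3% | 99.8% / 96% | 99% / 91% |
| 2% v 4% | 99.5% / 94% | 98% / 91% |
| 1% v 5% | 98% / 85% | 91% / 72% |
| 2% v 6% | 97% / 85% | 90% / 78% |
| 0% v 10% | 63% / 26% | 23% / 5% |

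The last row can be checked by hand. With no hotel events, Fisher at 49 per arm needs at least 6 wilderness events, and P(X ≤ 5) for Bin(49, 0.10) = 0.635. Pearson needs at least 4, and P(X ≤ 3) = 0.265.

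**5. What zero events would show.** With 0 of 49 in one arm, the exact two-sided 95% upper limit is 1 − 0.025^(1/49) = 7.3% (the one-sided 95% limit is 5.9%). With 0 of 75 it is 4.8%. For 0 v 0, the Newcombe 95% CI for the risk difference is −7.3 to +7.3 percentage points at 49 per arm and −4.9 to +4.9 at 75.

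**6. What a margin-based claim would need.** Approximately, n per arm = 2p(1 − p)(1.960 + 0.842)² / margin², at one-sided 0.025, 80% power and equal true rates. The rates and margins are assumptions, and the normal approximation is rough at such low rates.

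| True rate in both arms | Margin 2 points | 3 points | 5 points | 10 points |
|---|---|---|---|---|
| 1% | 389 | 173 | 63 | 16 |
| 2% | 770 | 342 | 124 | 31 |

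About 49 evaluable per arm could exclude only a large excess.

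**The case against.** **More than the one rule is planned.** The protocol article commits to an exposure-adjusted RR with 95% CI and to describing the number, seriousness, intensity and types of AEs, so a 5 v 0 split would be visible to readers. This stands, and part of the remedy is already in place. But the RR is for any AE and is tied to no margin, and neither analysis replaces the definition of equal safety. If the ratio were applied to serious AEs with none in one arm, it would be zero, infinite or undefined without a correction.

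**Safety is not a confirmatory outcome.** The rule affects no primary estimate, the trial is described as low risk, and a statistical analysis plan is still to be finalised. This is true and limits the damage. It does not make the point a detail left to that plan: the protocol article itself states the decision rule, and a plan that followed it would carry the error forward.

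**The rule is not blind to everything.** A reader might infer that it is met whatever the truth. The figures do not support that. For 0% v 10% it flags a difference 37% (Fisher) to 74% (Pearson) of the time at 49 per arm, and 77% to 95% at 75.

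**Relatedness.** A reader might also infer that only events judged related count, and that relatedness is judged knowing the arm. The safety evaluation does refer to "types of AEs that are evaluated to be certain, probable/likely or possibly related to the study programmes", but the sentence defining equal safety carries no such limit, so the text is ambiguous. Who judges relatedness, and with what knowledge, is not stated. Neither inference is part of the point made here.

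**Conclusion.** The defect is real and lies in the wording of the protocol article: non-significance is defined as equality, with no margin, in a trial not sized for serious AEs. At about 49 per arm, a doubling or tripling of an assumed 1% to 2% risk would be called equal safety 97% to nearly 100% of the time by Fisher and 85% to 99% by Pearson. With 75 per arm the ranges are 90% to 99.8% and 78% to 97%.

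This rests on three assumptions. Serious-AE rates are low, as the pilot's zero among 42 suggests but does not prove. Loss before the start is about 34.5%. The comparison is a person-level Fisher or uncorrected Pearson test, without the planned exposure adjustment. The logical fault does not depend on any of them; they settle only how often it would mislead.

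**What to change.** Delete the definition of equal safety as a non-significant difference, and replace it along these lines:

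- For serious AEs, report the number of participants affected per arm and the risk difference with a 95% CI that is valid with zero events (for example Newcombe's). This is in addition to the exposure-adjusted RR with 95% CI already planned for AEs.
- State that serious AEs are compared regardless of judged relatedness, with related AEs as a supporting table.
- Claim equal safety only if the upper 95% limit for the wilderness-minus-hotel difference lies below a margin that is justified and fixed before database closure. Otherwise report the upper limit and make no equality claim.

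The cost is wording in the protocol and the statistical analysis plan; recruitment, the interventions and data collection do not change. The downside is that the trial will probably be unable to claim equality on serious AEs and will have to state how large an excess it could not exclude.
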